### Analysis of end points

#### Primary end point analyses

The primary end points will be efficacy of the GDm-health system to achieve glycaemic control compared between groups. The results will be reported as a comparison between the two groups of change over time of BG level. The complete data form a complex longitudinal data set, over gestational age. A mixed-model analysis will be carried out on the data of the glucose level. The BG is measured six times per day according to the prescribed schedule, and levels of the multilevel analysis will be time point, gestational age and patient. In addition to the repeated measurements of BG, patient covariates (age, body mass index (BMI), gestation at recruitment, ethnic group) will be included in the model as fixed effects.

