**Methods and analysis:**

Women with confirmed gestational diabetes in a current pregnancy are individually randomised to either the GDm-health system and half the normal clinic visits or normal clinic care. Primary outcome is mean BG in each group from recruitment to delivery calculated, with adjustments made for number of BG measurements, proportion of preprandial and postprandial readings and length of time in study, and compared between the groups. The secondary objective will be to compare the two groups for compliance to the allocated BG monitoring regime, maternal and neonatal outcomes, glycaemic control using glycated haemoglobin (HbA1c) and other BG metrics, and patient attitudes to care assessed using a questionnaire and resource use.

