## Methods and analysis

### Objectives

The primary objective of this trial is to evaluate the efficacy of monitoring BG in pregnancy using remote glucose monitoring (GDm-health) compared to standard clinic care. Efficacy will be determined by comparing BG control as determined by mean BG readings from recruitment until delivery between the intervention and the control group. The secondary objective will be to compare the two groups for compliance to the allocated BG monitoring regime, maternal and neonatal outcomes, glycaemic control using glycated haemoglobin (HbA1c) and other BG metrics, and patient attitudes to care assessed using a validated questionnaire^20^ and resource use.

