### Accrual and analysis

#### Sample size

The four published randomised trials that investigated the effect of a telehealth intervention on mean BG control in pregnancy reported SDs between 0.2 and 1.2 mmol/L. The lower value was from a very small study (n=19) conducted in 1996.^22^ The range of SD for mean BG in the three relatively large studies (n>30) was 0.5–1.2 mmol/L.^13^
^15^
^17^ This indicates that we do not yet have a precise estimate of the likely SD in mean BG, making sample size calculation challenging. We therefore pragmatically decided to assume an SD of 0.8 mmol/L for the mean BG level at the end point. Thus, with 100 patients in each arm, we will be able to detect a difference between the arms of 0.32 mmol/L, with power of 80% and a significance level of 0.05.

The multilevel analysis we propose has not been conducted in any of the previous studies and will use all the data from recruitment to delivery. Thus, the difference in BG between the arms at the study end point will be estimated more precisely compared with a trial that uses a comparison of mean BG at the end point alone or a mean of all readings. Therefore, the calculation given provides a conservative estimate of the effect size that could be detected.

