## Discussion

This trial will give valuable information regarding the role of remote BG monitoring in women with GDM. We will determine the efficacy of remote monitoring in pregnant women with GDM compared to conventional care and provide an objective assessment of the potential value of the technology in impacting outcomes including BG control, patient satisfaction and resource use. Severe adverse clinical outcomes, such as shoulder dystocia or neonatal hypoglycaemia, associated with GDM are relatively uncommon among women receiving management. Therefore, we will use a measure of glycaemic control as our primary outcome as this has been shown in large studies^3^
^4^ to correlate with risk of adverse outcomes.

Selecting a clinically relevant summary measure of glycaemic control in pregnancy is challenging owing to the progressively changing physiology of glucose regulation in the third trimester of pregnancy. We plan to assess the difference in overall mean BG between the two groups as the primary outcome for this trial; however, an intended objective will also be to assess and compare other summative metrics of glucose control including HbA1c, changes in BG over gestation and changes in BG in relation to meal times between the two groups. This will enable us to select a valid primary outcome measure, with known SD and estimation of effect size, to allow calculation of sample size for a future definitive trial.

One of the criticisms of the vast number of health-related ‘apps' now available is that there is currently little empirical evidence to support their use. Most ‘apps' have been developed by the commercial sector or by patient groups, but few are integrated within the healthcare system. We hope that the results of our trial will provide some of the first robust findings on the potential for integrated remote monitoring systems to affect patient outcomes.

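### The primary contrast is stated inconsistently: overall mean BG in the objectives, change over time in the analysis section, and level at the end point in the sample size.

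*Protocol article*

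**What the plan says.** All references are to the protocol article.

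- **Overall mean.** The Objectives determine efficacy by "comparing BG control as determined by mean BG readings from recruitment until delivery between the intervention and the control group". The abstract agrees: "Primary outcome is mean BG in each group from recruitment to delivery calculated, with adjustments made for number of BG measurements", together with the preprandial/postprandial proportion and the time in study. The Discussion states: "We plan to assess the difference in overall mean BG between the two groups as the primary outcome for this trial". The strengths and limitations list says the same.
- **Change over time.** The section on primary end point analyses describes a mixed model for the glucose readings and then says: "The results will be reported as a comparison between the two groups of change over time of BG level". Its fixed-effect covariates are age, BMI, gestation at recruitment and ethnic group. The Discussion places change over gestation elsewhere, among "other summative metrics of glucose control including HbA1c, changes in BG over gestation and changes in BG in relation to meal times".
- **Level at the end point.** The Sample size section assumes an SD of 0.8 mmol/L for mean BG at the end point. It derives a detectable difference of 0.32 mmol/L with 100 women per arm, 80% power and a significance level of 0.05. It then argues that, with the multilevel model, "the difference in BG between the arms at the study end point will be estimated more precisely" than by comparing end-point means alone or the mean of all readings, and so calls the calculation conservative.

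**The concern.** An average level over follow-up, a difference in how BG changes over follow-up, and a difference at the end of follow-up are three different parameters. One mixed model can produce all of them, so the protocol has to say which one carries the trial's conclusion. The section that fixes the primary analysis names a contrast that the Discussion treats as additional, and the sample size is argued for neither that contrast nor the overall mean.

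Two things are at stake. An analyst who follows the analysis section and one who follows the Objectives could reach different headline results from the same data. Also, the stated power and the claim that it is conservative do not describe the result that is to be reported.

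**Working it through.** **Inputs from the Sample size section:** 100 per arm, SD 0.8 mmol/L, difference 0.32 mmol/L, power 80%, significance level 0.05. The cited SD range from the larger earlier trials is 0.5 to 1.2 mmol/L. Sidedness is not stated. A one-sided test would need only 78 per arm, so the stated figure is two-sided.

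**Step 1: reproduce the plan's figure.** For a two-sample comparison of means with n = 100 per arm, the standard error is SD × √(2/100).
- At SD 0.8: SE = 0.8 × 0.1414 = 0.1131.
- Detectable difference = (1.960 + 0.842) × 0.1131 = 0.317, which rounds to the stated 0.32.
- Power at 0.32 = Φ(0.32/0.1131 − 1.960) = Φ(0.868) = 80.7% (80.4% with the noncentral t on 198 degrees of freedom).

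The arithmetic is right. It is arithmetic for a difference in level, in mmol/L.

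**Step 2: constant shift (assumed shape).** Suppose the intervention lowers BG by 0.32 soon after randomisation and the gap then stays constant.
- Level contrast: difference 0.32, power 81% at SD 0.8.
- Linear change-over-time contrast: the expected difference is zero, so a two-sided 5% test rejects about 5% of the time.

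**Step 3: linear divergence (assumed shape).** Suppose the arms are equal at randomisation and diverge linearly to 0.32 at delivery, with readings spread evenly over follow-up.
- End-point contrast: difference 0.32, power 81% at SD 0.8.
- Overall mean contrast: difference (0 + 0.32)/2 = 0.16. At SD 0.8, power = Φ(0.16/0.1131 − 1.960) = Φ(−0.546) = 29%. At SD 0.5, SE = 0.0707 and power = Φ(0.16/0.0707 − 1.960) = Φ(0.303) = 62%.

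The SD of a recruitment-to-delivery mean is not given. Applying 0.8 to it borrows the end-point figure, which is why the result at 0.5 is also shown.

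**Step 4: change over time read as simple change from baseline.** With SD 0.8 at both times and within-woman correlation ρ, the SD of change is 0.8 × √(2(1 − ρ)). The document gives no ρ, so these values are assumptions.

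| ρ | SD of change | Power at 0.32 | Per arm for 80% |
|---|---|---|---|
| 0.3 | 0.947 | 67% | 138 |
| 0.5 | 0.800 | 81% | 99 |
| 0.7 | 0.620 | 95% | 59 |

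Power for a change contrast can therefore be lower or higher than stated. The document gives neither the correlation nor a slope SD needed to say which.

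**Step 5: detectable difference in level over the cited SD range.** SD 0.5: 2.802 × 0.5 × 0.1414 = 0.20 mmol/L. SD 1.2: 2.802 × 1.2 × 0.1414 = 0.48 mmol/L.

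**The case against.** The strongest reply is that the primary outcome is named consistently as mean BG in four places, that the Sample size section declares no primary end point, and that the conflict comes down to one loose sentence in the analysis section. It is also true that the sentence speaks of change and does not specify a linear group-by-time test. Where a rate is meant, for HbA1c in the secondary analyses, the article says so. The trial has no interim analyses, and analyses are to be blinded to allocation group, which limits the scope for choosing among results.

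Much of this stands. The count does favour overall mean BG, which is why the fix adopts it, and the 5% figure depends on a linear contrast and an almost immediate effect. The contradiction remains, because the outlying sentence is the one that says what will be reported as the primary result. Nor can the sample-size wording be read as end point in the sense of outcome, since it sets the end point apart from the mean of all readings. A separate analysis plan could supply detail, but it could not follow both statements.

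A reader might also infer that the slope test will have inflated type I error, because the article says "levels of the multilevel analysis will be time point, gestational age and patient" and mentions no woman-specific slope. The document does not support that. It does not state a random-intercept-only model, and the full random-effects structure is commonly left to the analysis plan. Nor does it follow that the preprandial/postprandial mix is uncontrolled: the abstract lists its proportion among the adjustments. What stands is that the adjustments in the abstract and in the analysis section differ.

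**Conclusion.** The inconsistency is real and concerns the trial's headline result. Overall mean BG is primary in four places, change over time is what the primary analysis section will report, and the level at the end point is what the trial was sized on. The stated 80% power, reproduced at 80.7%, and the conservative claim apply to a difference in level and have no stated basis for a change-over-time contrast.

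The power figures of 5%, 29% and 62% are illustrations. They assume particular effect shapes, and the last two also assume an SD for the overall mean that the document does not give. A reader might infer from them that the trial is underpowered. That does not follow: the sample size reproduces, and power for change over time could fall on either side of 80% depending on quantities not reported.

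**What to change.** 1. **Primary end point analyses:** state that the primary result is the adjusted between-arm difference in mean BG from recruitment to delivery, estimated from the mixed model.
2. **Adjustments:** reconcile the list in the abstract (number of readings, preprandial/postprandial proportion, time in study) with the list in the analysis section (age, BMI, gestation at recruitment, ethnic group), and include preprandial/postprandial time point explicitly.
3. **Other contrasts:** label the change-over-time and end-point contrasts secondary, in line with the Discussion.
4. **Sample size:** restate and justify the SD, the detectable difference and the conservative claim for the recruitment-to-delivery mean. Moving the primary contrast without re-tying the SD would leave the mismatch in place. Show the detectable difference over the cited SD range: 0.20 mmol/L at SD 0.5 to 0.48 mmol/L at SD 1.2.

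The cost is a wording change in the protocol and any analysis plan before unblinding, with no operational consequence.

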### Source and screening of potential participants

Pregnant women found to have GDM will be assessed by a specialist diabetes midwife. All women will be taught how to test and record their BG levels and asked to keep a food diary for 1 week. All women will be given an information leaflet about the study at their first visit. One week later, they will be assessed again in the specialist diabetes midwife clinic. At this visit, women will be given dietary advice and have baseline measurements taken (box 1). Those requiring insulin treatment for their gestational diabetes will start treatment and be referred to the consultant-led antenatal diabetes clinic. Those not requiring pharmacological treatment or only requiring oral hypoglycaemic therapy (metformin or glibenclamide) and that meet the inclusion/exclusion criteria listed in table 1 will be eligible for the trial and invited to participate. Figures 1 and 2 summarise the study selection process.
Box 1Measurements takenThe baseline measures at recruitment:
Gestational age (days)Weight (kg)AgeParityEthnicitySmoking statusHighest education levelHbA1c (%)Medication (type and dosage)Blood pressureOral glucose tolerance test resultMeasures taken at subsequent clinic visits
Glycated haemoglobinChanges to medicationWeight (kg)Maternal and fetal outcomes
Gestational age at delivery (days)Birth weight (kg)Mode of delivery (vaginal, caesarean, assisted)Severe perineal injury (binary)Shoulder dystocia/birth injury (binary)Neonatal hypoglycaemia (binary)Neonatal hyperbilirubinaemia (binary)Diagnosis of maternal pregnancy-induced hypertension or pre-eclampsia (binary)
Admission to higher level of care (maternal) (binary)Admission to higher level of care (neonate) (binary)

**Table 1 BMJOPEN2015009702TB1:** Inclusion and exclusion criteria

Inclusion criteria	Exclusion criteria
An abnormal glucose tolerance test in this pregnancy (as defined by IADPSG recommendations^6^)	Impaired cognitive function such that she is unable to operate m-health equipment
Women not requiring pharmacological treatment at recruitment	Any evidence of fetal compromise
Women started on oral hypoglycaemic therapy at recruitment	Known risk factors for obstetric complications, other than obesity and gestational diabetes
Willing and able to give informed consent for participation in the study	Gestational diabetes requiring immediate insulin treatment
Female aged between 18 and 45 years	Twins or higher order pregnancy

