### Randomisation

Participants will be randomly allocated to one of two groups using a partial minimisation procedure. This will adjust the randomisation probabilities between groups to balance important covariates including gestational age at recruitment (<28 or ≥28 weeks), weight at randomisation (<90 or ≥90 kg) and ethnic group (Caucasian/white or other) using Oxford University Primary Care Clinical Trials Unit randomisation system—Sortition.^21^ This is an online randomisation programme with secure access for predesignated individuals (investigators from the trial). Randomisation will be carried out at the time of recruitment by the investigators by logging onto the system to obtain the next allocation. Women will be randomised individually into the study in an equal ratio of standard care (control) to remote monitoring (intervention). Both groups will use the same glucose meter (OneTouch UltraEasy, LifeScan, Inc).

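### The primary mixed model adjusts for no baseline measure of glycaemia, although HbA1c, OGTT result and medication are recorded at recruitment: a loss of efficiency for mean BG, not a bias

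*Protocol article*

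**What the plan says.** The section on primary end point analyses specifies a mixed model for repeated BG readings in which "patient covariates (age, body mass index (BMI), gestation at recruitment, ethnic group) will be included in the model as fixed effects". The abstract describes the primary outcome as mean BG "with adjustments made for number of BG measurements, proportion of preprandial and postprandial readings and length of time in study". None of those further adjustments is a baseline measure of glycaemia.

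Box 1 lists HbA1c, medication (type and dosage) and the OGTT result among the measures taken at recruitment. Entry treatment is mixed by design: "Those not requiring pharmacological treatment or only requiring oral hypoglycaemic therapy (metformin or glibenclamide" are the women invited. Minimisation uses "gestational age at recruitment (<28 or ≥28 weeks), weight at randomisation (<90 or ≥90 kg) and ethnic group (Caucasian/white or other", so neither starting glycaemia nor entry treatment is balanced by the allocation procedure.

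The protocol describes the primary contrast in two ways. The primary end point section says: "The results will be reported as a comparison between the two groups of change over time of BG level". The Discussion says: "We plan to assess the difference in overall mean BG between the two groups as the primary outcome for this trial". The abstract and the Objectives also name mean BG, and the Sample size section powers the trial on mean BG level.

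**The concern.** When the outcome is glucose, a woman's glycaemia at entry is a natural candidate to explain part of the variation between women. The protocol records three such measures and uses none of them, either in the allocation or in the primary model. The secondary HbA1c model has its own list, which adds haemoglobin at recruitment, so covariates are evidently being chosen model by model. The four in the primary model therefore read as a stated choice.

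What is at stake is the width of the interval on the primary contrast. The Sample size section concedes that the SD is poorly known (0.5 to 1.2 mmol/L in the larger earlier trials), so precision that can be had from data already in hand is worth taking.

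**Working it through.** **Inputs.** From the Sample size section: SD 0.8 mmol/L, 100 women per arm, detectable difference 0.32 mmol/L, power 80%, significance level 0.05. Sidedness is not stated. Assumed: ρ, the correlation between baseline glycaemia and a woman's mean BG beyond age, BMI, gestation and ethnic group. The documents give no value.

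**Step 1: reproduce the plan's figure.** Two-sided, normal approximation:

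- Detectable difference = (1.960 + 0.842) × 0.8 × √(2/100) = 0.317 mmol/L, which agrees with the stated 0.32.
- Power at 0.32 = Φ(0.32 / (0.8 × √(2/100)) − 1.960) = Φ(2.828 − 1.960) = 80.7%.
- Women per arm for 0.32 = 2 × 2.802² × 0.8² / 0.32², rounded up = 99. A one-sided test would need 78, so two-sided 0.05 was used.

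**Step 2: adjust for baseline glycaemia when the contrast is mean BG.** The residual SD becomes 0.8 × √(1 − ρ²). Putting this into the same formulas gives:

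| ρ (assumed) | Residual SD | Detectable difference (mmol/L) | Power at 0.32 | Women per arm for 80% power |
|---|---|---|---|---|
| 0 | 0.800 | 0.317 | 80.7% | 99 |
| 0.2 | 0.784 | 0.311 | 82.3% | 95 |
| 0.3 | 0.763 | 0.302 | 84.3% | 90 |
| 0.5 | 0.693 | 0.274 | 90.4% | 74 |
| 0.6 | 0.640 | 0.254 | 94.2% | 63 |

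At ρ = 0.5 the information equals that from 100 / (1 − 0.25) = 133 women per arm without adjustment, or 33 more per arm. The proportional gain √(1 − ρ²) does not depend on the SD. The unadjusted detectable difference does: it runs from 0.198 to 0.475 mmol/L for SDs of 0.5 to 1.2.

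**Step 3: chance imbalance.** With 100 per arm, the standardised baseline difference has standard error √(2/100) = 0.141 SD. About one trial in 20 will therefore be out by 1.96 × 0.141 = 0.28 SD or more. An imbalance of that size moves an unadjusted mean-BG estimate by ρ × 0.8 × 0.28, about 0.07 mmol/L at ρ = 0.3 and 0.11 at ρ = 0.5.

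**Step 4: the same adjustment when the contrast is a slope.** This was simulated with 200 women, nine equally spaced time points, random intercepts and slopes, 400 replicates, and a baseline covariate that predicts level but not slope. The standard error with the covariate, divided by that without it, was:

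| ρ | Mean difference | Slope difference |
|---|---|---|
| 0.3 | 0.957 | 1.003 |
| 0.5 | 0.869 | 1.002 |

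The gain belongs to the mean-BG contrast. A baseline main effect adds nothing to a pure slope contrast unless baseline glycaemia also predicts the slope.

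**The case against.** The strongest objection is that the section containing the covariate list also describes the contrast as change over time, for which Step 4 shows no gain. That stands as a condition on the size. It does not remove the point, because the abstract, the Objectives and the Discussion name mean BG and the trial is powered on mean BG level.

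Second, ρ may be low. Women needing immediate insulin and those whose OGTT suggests pre-existing diabetes are excluded, which narrows the baseline range. Both arms are managed to common targets. The OGTT may be done at 16 or at about 28 weeks, so its lag to the outcome varies. All this stands. It is why ρ = 0.2, where power rises by less than two percentage points, belongs in the range, and why no single value should be quoted as the gain.

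Third, a reader might infer that the week of home testing before the baseline visit is a covariate already in hand, since "All women will be taught how to test and record their BG levels and asked to keep a food diary for 1 week". The documents do not support this. Box 1 does not list those readings. Under Measures of BG, control data come from scanned charts checked against a meter download at the end of pregnancy, and intervention data come from the website. Intervention women are given the phone and application as part of their allocated care, and nothing says that earlier readings reach the website. Availability could differ by arm, and a missing-value indicator would then be partly confounded with treatment.

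Fourth, the covariate list is not declared exhaustive, and an unseen analysis plan may extend it. If that plan already adds these measures, the point is met. As published, the protocol names four covariates and leaves these out.

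**Conclusion.** The point holds as one of efficiency. The primary model uses no baseline measure of glycaemia although three are recorded at recruitment. For overall mean BG, adjustment would bring the detectable difference from 0.317 down to between 0.311 and 0.254 mmol/L, and power at 0.32 from 80.7% up to between 82.3% and 94.2%, for assumed ρ from 0.2 to 0.6. The omission is certain; the size of the gain is not, because it rests on an assumed ρ and on the contrast being mean BG.

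A reader might go further and infer that the treatment estimate is biased, or that the sample size is wrong. Neither follows. Randomisation keeps the unadjusted comparison valid, and its confidence interval already allows for chance imbalances such as those in Step 3. The sample size claims no gain from covariates and reproduces as stated.

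**What to change.** - Add baseline HbA1c, fasting OGTT glucose and oral hypoglycaemic therapy at recruitment (yes/no) to the primary mixed model as prespecified fixed effects, using values recorded before allocation.
- State a simple rule for missing baseline values, such as imputing the overall mean.
- Reconcile the change-over-time wording with overall mean BG and name one primary contrast. If slopes are chosen, no precision gain should be claimed from these main effects.
- Include pre-randomisation BG only if it is confirmed to be captured in the same way in both arms.

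The first two items cost a few lines in the analysis plan and about three degrees of freedom in 200 women. They need no new data and no change to the sample size.
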